## Loss to Follow-up

If any of the trial patients are lost to follow up, contact will initially be attempted through the school and parent address, otherwise missing data will be imputed using median values by treatment group.

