## Sample Size

At Stage One, our previous studies indicate that a sample of 600 participants will be needed to identify an adequate number of eligible participants* for the intervention study, for which power calculations have been carried out (see below). This number of Stage One participants will also provide sufficient variance on all secondary outcome measures to ensure valid correlational analyses between these.

*Recruits to Stage Two must show ‘room for improvement’ on the main primary outcome (i.e. scoring within the lowest tertile on age-standardised measures of reading).

Following the only previous randomized controlled study to assess reading ability, power calculations were performed to estimate likely group sizes ([name] & [name], 2005)). These indicated that with significance set at 5% and power at 90%, groups of 180 (i.e. a total n of 360) would be required, based on our standardized reading change. Other outcomes would have required smaller sample sizes.

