## Analysis Plan

The study will be analysed and reported following the ‘CONSORT’ guidelines (Consolidated Standard of Reporting Trials) (Moher, 2001).

On completion of the study post-intervention change score data from all children participating in Stage Two will be analysed on an intention to treat basis. Since the original protocol required that children be below the 20th centile on a standardized word reading test, ITT analysis of post-intervention change score data on these children will also be carried out. To further assess the importance of severity of reading impairment at baseline, similar analyses will be performed on children whose reading was assessed ≤ 10% level.

Missing data will be handled by imputing median values for missing data by treatment group.

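### Filling missing outcomes with the arm median and analysing them as observed makes standard errors too small, so the 5% test runs above 5%, by an amount set by an unstated loss rate

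*Protocol*

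**What the plan says.** The rule stands in two sections of the protocol. The Analysis Plan says: "Missing data will be handled by imputing median values for missing data by treatment group". Under Loss to Follow-up, after attempts to contact the family, "otherwise missing data will be imputed using median values by treatment group".

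The imputed values enter the main comparison, because the Analysis Plan states that "post-intervention change score data from all children participating in Stage Two will be analysed on an intention to treat basis". No variance correction, multiple imputation or sensitivity analysis accompanies the rule. The method is therefore fixed here and not left to a statistical analysis plan.

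Two things that decide the size of the problem are not stated: the expected loss rate, and whether the median is taken of the post-test or of the change score.

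**The concern.** A median carries no information about the child who is missing. Giving it to every missing child in an arm has two effects on the standard error, both in the same direction: the sample variance falls because the added values have almost no spread, and the divisor stays at the full sample size although fewer children were measured. P-values come out too small and confidence intervals too narrow. The trial sets out to confirm or refute a benefit, and the error runs towards false positives.

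The rule also ignores the child's own baseline. If the post-test is imputed, a weak reader who is lost is credited with an artificial gain, and a strong reader with an artificial fall. When the lost children are mostly weak readers and one arm loses more of them, these artefacts do not cancel.

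**Working it through.** **Inputs.** From the protocol: 180 children per arm, 5% significance and 90% power (Sample Size); change scores of all Stage Two children by intention to treat, and arm-median imputation (Analysis Plan). Assumed, because the protocol is silent: a two-sided test and missing fractions *m* of 5% to 20%.

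**The plan's own figure.** No effect size or SD is given, so 180 per arm can only be back-solved. With n = 2(1.960 + 1.282)²/d², d = 0.342 SD gives 2 × 10.51/0.117 ≈ 180. This is not a confirmation. The point does not depend on it, since *n* and the SD cancel below.

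**Standard error used by the test.** With a fraction *m* set to a central constant, the arm variance is about (1−m)s², so the naive SE is s√(1−m)·√(2/n).

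**True standard error.** The imputed arm mean is (1−m) × observed mean + m × observed median, based on n(1−m) children. For normal data the variance of the median is π/2 times that of the mean, and their covariance equals the variance of the mean. The true SE is therefore s√(2/(n(1−m)))·√(1 + m²(π/2 − 1)).

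**Ratio and actual level.** Ratio = (1−m)/√(1 + 0.571m²), and actual level = 2[1 − Φ(1.96 × ratio)].

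- m = 0.10: ratio 0.90/√1.0057 = 0.897; 1.96 × 0.897 = 1.76; level 7.9%.
- m = 0.20: ratio 0.80/√1.0228 = 0.791; 1.96 × 0.791 = 1.55; level 12.1%.

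**Simulation with no true effect** (180 per arm, equal random loss, normal data). Change-score and observed-only columns: 40,000 runs per row. Post-test column: 20,000 runs per setting, baseline–post correlation 0.5 to 0.9, except where marked.

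| Missing in each arm | Formula, change score imputed | Simulated, change score imputed | Simulated, post-test imputed, unadjusted change | Observed change scores only |
|---|---|---|---|---|
| 5% | 6.3% | 6.3% | 5.2%* | 5.1% |
| 10% | 7.9% | 8.0% | 6.3–6.6% | 5.0% |
| 15% | 9.8% | 9.7% | not run | 4.9% |
| 20% | 12.1% | 11.9% | 8.1–9.1% | 4.9% |

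*4,000 runs at correlation 0.7, Monte Carlo error about 0.35 points.

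Simulated naive and true SEs with the change score imputed were 0.0999 against 0.1116 at 10% missing, and 0.0942 against 0.1187 at 20%. Heavy-tailed or skewed change scores gave 7.0–7.1% and 10.0–10.5% at 10% and 20%. Adjusting for baseline after imputing does not help: 7.6–8.0% and 11.9–12.5% if the change score was imputed, 8.0–8.3% and 12.1–14.3% if the post-test was.

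**Bias with no true effect, correlation 0.7, post-test imputed.**

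- Random loss of 10% against 20%: −0.003 SD, which is nil.
- Equal loss in both arms, more likely at low baseline: 0.00 SD.
- Loss of 10% against 20% and more likely at low baseline: about +0.06 SD, with type I error of about 12–14%. Weaker to stronger dependence on baseline gave +0.03 to +0.07 SD and 9–15%. The false effect favours the arm that loses more children.

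**The case against.** Five objections deserve an answer.

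**The loss rate is assumed.** A reader might infer that the test simply runs at 7–12%. The protocol does not support that. Those figures need 10–20% missing and imputation of the change score, and neither is stated. Reading and digit recall are tested at school and teachers supply their own ratings, so loss on these may be low, though that is also unproven. With 2–3% missing the level was 5.1–5.8%, hardly distinguishable from nominal. This limits the size; the direction of the error remains.

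**Children who stop treatment.** One might infer that a child who stops capsules is given the arm median. The sections on withdrawal and transfer say otherwise: follow-up generally continues after withdrawal from the intervention, evaluations are still requested, and transferred children are sought at the new school. The rule reaches only children with no post-intervention measure.

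**Bias.** One might infer bias whenever loss differs by arm or depends on baseline. With no true effect, neither alone produced any; both are needed together.

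**Observed cases are not a perfect comparator.** In that joint scenario, observed unadjusted change scores are also slightly off (−0.02 to −0.03 SD, 5.2–6.8% type I error). This stands, and is why the replacement should adjust for baseline.

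**Carrying the arm difference to missing children is not peculiar to medians.** Within-arm multiple imputation does so too under missing at random. The defect specific to the median rule is that it ignores both the uncertainty and the child's baseline.

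**Conclusion.** The rule is wrong as written. It understates the standard error for any outcome with missing values, in proportion to that outcome's own missingness; an outcome with complete data is unaffected.

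Under equal random loss and a two-sided test, the nominal 5% becomes about 6% with 5% missing and about 8% and 12% with 10% and 20% missing if the change score is imputed. It becomes about 6.5% and 8–9% at 10% and 20% if the post-test is imputed and unadjusted change is tested. The mechanism follows from the protocol alone; the size rests on the assumed loss rate and on which score is imputed.

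Bias of about 0.06 SD is a further possibility, conditional on post-test imputation and on loss that both differs by arm and depends on baseline. The protocol gives no evidence that such loss is expected.

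**What to change.** Delete the median-imputation rule under both Analysis Plan and Loss to Follow-up. State that the main test is an ANCOVA of observed post-intervention outcomes, adjusted for baseline score and for the minimisation factors sex and school. This holds the 5% level when loss depends on those covariates.

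Multiple imputation within arm, combined by Rubin's rules, and a delta-shift analysis may be added as sensitivity analyses. The delta-shift addresses loss that depends on the unseen outcome, which ANCOVA does not cover. Neither is needed to correct the error.

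The wording change is small, but it does move the main analysis from change scores with no stated adjustment to a baseline-adjusted model, and with up to fifty schools the plan should say how school is modelled. Confidence intervals become wider, as they should. For unadjusted change scores, the observed-only SE exceeds the naive imputed one by a factor √(1/(1−m))/√(1−m) = 1/(1−m), which is 1.05, 1.11 and 1.25 at 5%, 10% and 20% missing; baseline adjustment can recover part of this. No extra data are collected.

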# PHARMACOVIGILANCE

This trial will be conducted in accordance with the terms and conditions outlined in the Medicines for Human Use (Clinical Trials) Regulations 2004 (SI 2004/1031).

## Potential Risks and Benefits of Omega 3s

### Potential Risks

None are known. According to the US FDA, 3g per day of EPA + DHA is generally regarded as safe (GRAS). This study will use only 600mg.

Clinical studies of omega-3 supplementation in humans (adult and child volunteers and patients of both sexes and all ages) have not shown any consistent or serious short or long-term adverse side-effects.

Martek’s DHA is already is widely used in superior infant formulae. The FDA considers both DHASCO®-S and high-oleic sunflower oil to be “highly refined oils” that are not associated with allergic reactions.[[4]](#footnote-5)

### Potential Benefits

Clearly, benefits can never be guaranteed for individual participants in any research trial, but average intakes of DHA in the UK and other developed countries are widely acknowledged to be suboptimal for general health.(Hibbeln *et al* 2006) Adequate supplies of DHA are essential for optimal development and functioning of the brain and nervous system (particularly for vision), and for cardiovascular and immune health.

As noted above, preliminary RCT evidence from studies of healthy children has already shown improvements in attention, concentration and behaviour, and benefits for literacy skills. The aim of this study is to confirm and extend these findings.

# ETHICAL CONSIDERATIONS

## Ethical considerations

The study will abide by the principles of the World Medical Association Declaration of Helsinki (1964) and the subsequent revisions; Tokyo (1975), Venice (1983), Hong Kong (1989) and South Africa (1996). We consider the specific ethical issues relating to participation in this trial to be:

- Taking a placebo (dummy) treatment or the active (Omega-3) treatment.

There is no single, 'gold standard' treatment that is used to combat scholastic underachievement and/or behaviour problems in children. Those drugs that are sometimes prescribed for behaviour problems associated with ADHD have obvious and unpleasant side-effects that would make blinding difficult in any case, but more fundamentally, they are not an appropriate intervention for normal children who are simply underperforming at school. Placebo is therefore an appropriate comparator because (a) there is no standard treatment and (b) double-blinding enables the true treatment effect of DHA to be investigated.

- Case Report Forms and Assessments in English only

To provide appropriate translations of all trial documentation and assessments would require checks and validations of language, as well as a comprehensive review of cultural and linguistic influences on the study measures. The latter include age-standardised tests of literacy skills, which are likely to be affected by the primary language spoken. We unfortunately do not have the resources to fulfil these standards adequately and therefore must limit trial entry to children with English as a first language.

## Ethical Approval

The trial protocol is in preparation for submission to the Integrated Research Application System and to the Oxfordshire County Council Education Department (Appendix B).

## Informed Consent Process

Informed consent is a process initiated prior to an individual agreeing to participate in a trial and continues throughout the individual’s participation. Informed consent is required for all patients participating in coordinated trials. In obtaining and documenting informed consent, the investigators will comply with applicable regulatory requirements and adhere to the ethical principles that have their origin in the Declaration of Helsinki.

# TRIAL MONITORING

## Clinical Site Monitoring

### Direct Access to Data

Site monitoring may be deemed to be necessary as a result of central data checks. In order to perform their role effectively, the trial coordinator and others involved in Quality Assurance and Inspection may need direct access to primary data, eg school records, relevant medical reports etc. Since this affects the patient’s confidentiality, this fact is included on the Patient Information Sheet and Informed Consent Form.

### Confidentiality

Individual participant medical information obtained as a result of this study is considered confidential, and disclosure to third parties is prohibited with the exceptions noted below.

Electronic and paper record forms will be labelled with patient initials and unique trial registration and/or randomisation number. Verification of appropriate informed consent will be enabled by the provision of copies of participants’ signed informed consent/assent forms being supplied to the schools.

The Centre for Evidence Based Intervention (CEBI) will preserve the confidentiality of participants taking part in the study and The University of Oxford is registered under the Data Protection Act.

### Quality Assurance and Quality Control of Data

QA includes all the planned and systematic actions established to ensure the trial is performed and data generated, documented/recorded and reported in compliance with applicable regulatory requirements.

QC includes the operational techniques and activities done within the QA system to verify that the requirements for quality of the trial-related activities are fulfilled.

This trial will undergo a risk assessment, the outcome of which is likely to indicate that it is a low risk trial. As such, site visits will be conducted and source data verification performed if indicated to be required as a result of central monitoring processes. To this end:

- The Principal Investigators, the Trial Coordinator and other staff will attend the launch meetings for key staff from participating schools, which will incorporate elements of trial-specific training necessary to fulfill protocol requirements.
- The Trial Coordinator will verify that appropriate approvals are in place prior to initiation of a school, and to check that the relevant personnel have attended trial-specific training.
- The Trial Coordinator will check safety and compliance reporting rates between centres.
- The Trial Coordinator will monitor screening, recruitment and drop-out rates between schools.
- The Trial Coordinator will conduct data entry consistency checks and follow-up data queries.
- Independent oversight of the trial will be provided by the Trial Steering Committee, to which [name] will play a reporting role.

## Records Retention

The CEBI undertake to store originally completed record forms and separate copies of the above documents for up to a maximum of 3 years or until the University informs the investigators that the documents are no longer to be retained.

Arrangements will be made to ensure the continued storage of the documents, even if the investigators, for example, leave the University or retire before the end of required storage period. Delegation will be documented in writing, and the investigators will archive all relevant source documents so that the trial data can be compared against source data after completion of the trial (e.g. in case of inspection from authorities).

# INDEMNITY

Indemnity for this trial will be provided by the University of Oxford.

# FINANCIAL ARRANGEMENTS

These have been negotiated between the Research Services Office at Oxford University and Martek Biosciences

# The Trial Steering Committee will be consulted quarterly and its role will be to provide guidance and advice on the following topics:

- Recruitment
- Randomisation
- Trial progress
- Protocol amendments
- Ethics
- Budget
- Adverse events and serious adverse events

# PUBLICATIONS

It is anticipated that at least three strong academic papers will be forthcoming from this study: one on the primary outcomes (to address whether DHA improves child behaviour and learning); a second on the objective blood biochemical measures and their correlations with the outcome measures; and a third looking at the role of sleep in relation to DHA and its effects on behaviour and learning. The data generated should also provide material for further academic publications in addition to these major ones.

We will also produce briefer papers for the ‘trade press’ as well as website material for posting on the University of Oxford Centre for Evidence Based Intervention website, and any such materials will be available for Martek Biosciences Corporation to use as they see fit.

[name]

[name]

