## Objectives

The primary objective of this trial is to determine whether DHA (in a daily dose of 600 mg.) will improve the behaviour and learning of normal children aged 7-9 years in mainstream state schools who are underperforming according to nationally standardized tests (≤ 33rd centile in literacy skills) but who had no other significant learning difficulties according to their teachers.

Secondary objectives include determining (a) whether blood biochemical measures of fatty acid status are associated with behavioural and cognitive outcomes, and with sleep; and (b) whether DHA supplementation changes children’s sleep, and if so, whether this may mediate any changes in behaviour and learning.

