# TRIAL DESIGN

## Design

Stage One is an observational study of up to 600 underperforming children aged 7-9 years from the general school population. 360 children, whose assessment scores at Stage One indicate that they may benefit from the study intervention, will enter a

randomised controlled trial of DHA vs placebo for 16 weeks (fixed dose, parallel group study).

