## Secondary Endpoints

1. To assess whether levels of DHA or related fatty acids (assessed objectively via a pinprick blood sample) predict their learning, behaviour or sleep.
2. To assess whether any changes in behaviour or cognitive performance are associated with changes in objective measures of blood fatty acid status.
3. To assess whether any treatment effects on behaviour or cognition are mediated by changes in child sleep (measured subjectively in all participants and objectively in a subset).
4. To explore associations between child sleep and blood fatty acid status (at each timepoint, and with respect to changes following treatment).

.

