### Fingerprick blood measures to assess fatty acid status and compliance

A fingerprick blood test will be performed at baseline for children in Stages One and Two andat the end of the study for children in Stage Two, in order toassess levels of fatty acid including docosahexaenoic acid (DHA), arachidonic acid (ARA), and eicosapentaenoic acid (EPA). Analysis of the fatty acids levels will be performed at Martek Biosciences Corporation, and the investigators will remain blinded to these until treatment codes are unlocked.

The fatty acid data will be used to verify compliance and to determine the relationship between levels of fatty acids in the blood and specific endpoints.

This blood test will be optional and will appear as a separate item on the consent form, but every effort will be made to maximize participation.

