# STATISTICAL CONSIDERATIONS

## Method of Randomisation

Randomisation of children in stage two will be performed centrally at the Centre for Statistics in Medicine in Oxford (CSM) using dedicated computer software. Following recruitment and consent, participants’ details will be faxed to the CSM. The randomisation programme will include a minimisation algorithm to ensure balanced allocation of participants across the treatment groups for school (to allow for any sociodemographic/school differences) and sex of the child (an important prognostic factor). The first 36 patients (10%) will be allocated randomly without the minimisation factors to avoid predictability. The minimisation algorithm will be applied with an allocation ratio that is not fully deterministic. Fifteen percent of the sample will be randomly selected to use the objective sleep monitors (allowing for some refusals). The statistician carrying out the randomisation will have no direct contact with participants so allocation will be totally independent of patient recruitment.

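### The protocol says the Stage One sample makes the fatty-acid correlations valid, but sample size does not remove confounding, and school, social background and sex are allowed for only in the randomised stage

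*Protocol*

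**What the plan says.** Secondary Endpoints sets the question: "To assess whether levels of DHA or related fatty acids (assessed objectively via a pinprick blood sample) predict their learning, behaviour or sleep". Research Questions and the Stage One list under Outcome Measures also use *predict*. Objectives words the same aim more softly: "whether blood biochemical measures of fatty acid status are associated with behavioural and cognitive outcomes, and with sleep".

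Two places name a method, and in both it is correlation. Sample Size says the Stage One number will give "sufficient variance on all secondary outcome measures to ensure valid correlational analyses between these". PUBLICATIONS plans three papers, of which one is "a second on the objective blood biochemical measures and their correlations with the outcome measures". Analysis Plan deals with Stage Two change scores and missing data and says nothing about the Stage One associations.

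On background factors, Method of Randomisation minimises on "school (to allow for any sociodemographic/school differences) and sex of the child (an important prognostic factor"), which applies to Stage Two only. Study Populations adds that sex differences will be explored, without saying how. Demographics are collected from parents at baseline.

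On numbers, Design says: "Stage One is an observational study of up to 600 underperforming children aged 7-9 years from the general school population". Protocol Summary allows up to fifty schools. The fingerprick section says: "This blood test will be optional and will appear as a separate item on the consent form".

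**The concern.** Nobody is allocated to a blood DHA level in Stage One. Among children who do not take supplements, baseline DHA reflects diet, and diet may plausibly vary with family background, as may reading, behaviour ratings and sleep. A correlation that ignores background therefore mixes the two. More children narrow the confidence interval around the mixed quantity; they do not move it to the right place. Because this is bias, a larger sample makes a spurious result more likely to reach significance.

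The protocol recognises the relevant factors, but provides for them only where randomisation already protects the comparison. Children in one school, some rated by the same teacher, are also not independent, and nothing is said about this for Stage One.

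At stake is the content of one of the three planned papers, and of the lay material that PUBLICATIONS plans and makes available to the supplier.

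**Working it through.** **The protocol's own figure.** The 600 cannot be reproduced for this purpose. Sample Size rests it on previous studies and on finding enough children for Stage Two. It gives no correlation, significance level or power for the associations.

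**Inputs from the protocol.** Up to 600 children; up to 50 schools; blood sampling optional, with uptake not given. At the two ceilings, m = 600/50 = 12 children per school. Smaller n is shown because 600 is a maximum.

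**Assumed inputs.** No true association between DHA and the outcome. One background factor correlates a with DHA and b with the outcome. Two-sided 5% test. The documents give neither a nor b, so a range is shown.

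**Confounding.** With a zero partial correlation, the unadjusted correlation is r = a × b. By Fisher's z, the chance of significance is

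P = Φ(atanh(r)·√(n−3) − 1.96) + Φ(−atanh(r)·√(n−3) − 1.96).

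Example, a = b = 0.3 and n = 600: r = 0.09, atanh(r) = 0.0902, √597 = 24.43, product 2.205, so P = Φ(0.245) + a negligible term = 0.597.

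| a = b | spurious r | n = 600 | n = 360 | n = 300 |
|---|---|---|---|---|
| 0.2 | 0.04 | 0.165 | 0.118 | 0.106 |
| 0.3 | 0.09 | 0.597 | 0.400 | 0.343 |
| 0.4 | 0.16 | 0.976 | 0.862 | 0.794 |

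At a = b = 0.15 and n = 600, P is 0.085. The smallest correlation significant at 5% is 0.080 at n = 600 and 0.113 at n = 300.

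A simulation with 4000 repeats at n = 600 gave unadjusted rates of 0.166 (a = b = 0.2) and 0.602 (a = b = 0.3). After adjustment for the background factor the rates were 0.053 and 0.050.

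**Clustering by school.** The variance of a correlation is inflated by about 1 + (m − 1) × ICC(DHA) × ICC(outcome). With m = 12 and both intraclass correlations (assumed) between 0.05 and 0.20:

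- both 0.05: 1 + 11 × 0.0025 = 1.03, effective n 584, true level of the 5% test 0.053
- 0.10 and 0.20: 1 + 11 × 0.02 = 1.22, effective n 492, true level 0.076
- both 0.20: 1 + 11 × 0.04 = 1.44, effective n 417, true level 0.102

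Over most of this range clustering matters less than even modest confounding.

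**The case against.** The strongest reply is that the protocol nowhere says the correlations are unadjusted. The line in PUBLICATIONS forecasts a paper; it is not an analysis specification. Correlational analysis can include partial correlation or regression, and covariates for a secondary question are commonly left to a statistical analysis plan, which is not shown. This stands as far as it goes: a reader might infer that the protocol commits to plain correlations over 600 children, and the text does not support that. Six hundred is a ceiling, and blood sampling is optional. What a later plan cannot repair is the sentence in Sample Size, which rests validity on number and variance.

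It can be said that *valid* there means only that there is enough spread to correlate. That is a possible reading, but the sentence is the only statement in the statistical section about these analyses, and it invites the wider one.

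A reader might also infer that a correlation will be reported as an effect of DHA. The protocol does not say so. Objectives speaks of association, and PUBLICATIONS gives the question whether DHA improves outcomes to a separate paper. Nor are all measures taken at one visit: parent forms come by post. Stage Two children are reassessed after 16 weeks, so some relations could properly be called predictive.

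Some protection exists. Reading, digit recall and Conners scores are age-standardised, and eligibility (lowest third in reading, state schools, English as first language, limits on fish and fish oil) may weaken the correlations assumed above. Finally, adjustment restores 5% in the simulation because it uses the very factor that creates the bias. The protocol does not list what the demographics contain, so real adjustment may be incomplete.

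**Conclusion.** The point holds in limited form. Sample Size is wrong to suggest that number and variance ensure valid correlational analyses. Correlation is the only method named for an unrandomised question, and factors the protocol itself calls important are provided for only in the randomised stage. The false-positive rates (about 17% and 60% at n = 600, 11% and 34% at n = 300, for correlations of 0.2 and 0.3 with each variable) rest wholly on assumed inputs and apply only if the analysis is in fact unadjusted. They show that modest confounding is enough to matter, not that it is present. The randomised comparison and the primary outcomes are unaffected.

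**What to change.** In Sample Size, remove the claim that the number of children ensures validity. State instead that baseline associations will be estimated by regression of each outcome on fatty-acid level, adjusted for sex, the parent demographics already collected and school, with standard errors that allow for school, and for age where the score is not age-standardised. Show unadjusted estimates alongside. Make PUBLICATIONS consistent with this.

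In Research Questions, Secondary Endpoints and the Stage One list under Outcome Measures, use *associated with* for baseline relations, as Objectives already does.

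The cost is wording; no new data are needed. Children without a returned demographics form will contribute less to the adjusted estimates, and confounding by factors not measured will remain, which the report should say.
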